### Data collection, classification and handling of missing or incomplete data

Part 1 measure responses will be securely transmitted electronically after completion by parent proxy to a central study database or manually entered for any responses on paper. Part 1 CHC data, including date of onset, are abstracted, categorized by organ system, and graded using the CTCAE v5.0 at the Data Coordinating Center, using previously described methods for identifying CHC in childhood cancer survivors [42]. Part 1 neurocognitive data are scored at the Neuropsychology Coordinating Center, with final scores entered in REDCap. Part 2 clinical outcome results are securely transmitted electronically from the COG site to a central study database and categorized by the Data Coordinating Center as ‘normal’ or ‘abnormal.’ Any missing tests recommended by clinical practice guidelines are noted as ‘incomplete.’ The availability of in-home, remote completion, loaner tablets, and mobile Wi-Fi hotspots, in addition to compensation, are expected to facilitate data collection and reduce data missingness. Results from parent proxy neurocognitive assessments are summarized and provided to families at no cost to further incentivize participation and to facilitate subject access to special needs services.

For DS control participants, outcome data are collected using identical measures to assess CHC in addition to parent proxy completion of an identical neurocognitive battery. Similar to DS-AL cases, medical outcomes are verified by medical record review after a medical release is obtained, including both birth defects and CHC (type, severity, date of onset). DS controls do not complete the NIH Toolbox assessment and do not submit a biological specimen.

### Statistical analyses

For Part 1 data, the prevalence for each CHC will be estimated and compared with published CHC prevalence and grading data from non-DS AL survivor cohorts using CTCAE criteria [10, 11, 43, 44]. We will then construct longitudinal data to power time-to-event analyses, using two modeling approaches [45] to account for time-varying independent variable (diagnosis with AL) effects on time to a dependent variable (CHC incidence and CHC-free survival). Subjects without a CHC event will be censored at the time of study enrollment (DS-AL) or update of CHC or neurocognitive data (DS controls). For all analyses, we will pool observations over equal length intervals of chronologic age to predict short term risk of CHC during each age interval. First, we will use pooled logistic regression to estimate OR, 95% CI, and p-values for association of ALL, AML, or any AL diagnosis with medical record-verified CHC, agnostic of time to CHC. Next, we will use stratified Cox models to refine associations of ALL, AML, or any AL diagnosis with CHC based on time to CHC incidence. Within each age interval, we will estimate the hazard ratios (HR), 95% CI, and p-values to report time-dependent effects of ALL, AML, or any AL diagnosis on CHC. All models will be adjusted for age, sex, race/ethnicity, and relevant cancer or DS characteristics.

For Part 1 neurocognitive data, we will determine both raw and standardized scores derived from age-based norms for all tests. Quantitative data will be summarized with descriptive statistics and correlational techniques. Given inherent challenges of interpreting age-normalized results in an intellectually disabled population, data will be evaluated for evidence of floor effects, i.e., an atypical left-shifted distribution of standard scores for measures where lower scores suggest lower skill ratings (Vineland, CCC-2) or a rightward shift for measures where higher scores indicate more behavioral issues (BRIEF-2, SCQ, NCBRF). Mean scores for each assessment will be compared between DS-AL survivors and DS controls, as well as between DS-AL subgroups and DS controls. The mean score for each test will be compared between the cohorts using a Student t-test (2-sided significance level of 0.05 and equal variance). If atypical score distributions restrict our ability to use parametric statistics, we will consider nonparametric approaches to group comparisons or score transformations to facilitate use of parametric modeling. In addition, we will utilize frequency comparisons, with scores dichotomized as clinically significant impairment yes/no according to manualized procedures (≤ 1.5 SD outside of the mean for the age-normative sample) and will compare the proportion of subjects ‘at the floor’ between DS-AL survivors, DS-AL subgroups, and DS controls.

For Part 2, the proportion of results that are ‘abnormal’ for each test will be detailed using descriptive statistics and compared between DS-ALL and DS-AML survivors.

For Part 3, we will use Cox regression to estimate the HR and 95% CI for number, severity, and type of CHC, as well as for neurocognitive deficits dichotomized as clinically significant impairment yes/no (≤ 1.5 SD outside of the mean for the age-normative sample) according to age at diagnosis, years off therapy, sex, race/ethnicity, diagnosis, and treatment exposures. We will use Cox regression to estimate HR and 95% CI for number, severity, and type of CHC by number of birth defects, as well as explore the role of DS-ALL susceptibility variants identified in our genome-wide assessment [46] on DS-associated CHC in survivors. All models will be adjusted for sex, genetic ancestry (estimated using the top 10 principal components), and age at diagnosis (years). We will determine genetically-estimated telomere length (TL) using methods described previously [47] and use a multivariable Cox proportional hazard model to estimate HR, 95% CI for the association between each of nine variants and risk for neurocognitive deficit ≤ 1 SD below the mean, considering the weighted and unweighted risk score from the number of risk alleles present and previously-published beta estimates. For flow-FISH analyses, TL ≤ 1 st percentile is considered ‘very short,’ as previously defined [48]. We will determine ORs for neurocognitive deficits ≤ 1.5 SD below the mean for a DS age-normative sample in subjects with TL > or ≤ 1 st percentile, adjusted for relevant covariates and treatment factors (e.g. ALL, AML). We will report 95% CI, p values using McNemar’s test (two-tailed p-value of 0.05 statistically significant).

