## Background

Survival from childhood and adolescent cancer has increased significantly in the past several decades, from under 50% in the 1970s to over 80% today [1]. This remarkable achievement has resulted in an exponential increase in the number of childhood cancer survivors living in the United States, projected to exceed 500,000 by this year [2]. However, the price of cure includes a significant burden of treatment-related morbidities. Seventy percent of adult survivors are estimated to suffer from one or more severe, disabling, or life-threatening chronic health conditions (CHC) or 'late effects' that significantly and negatively impact their quality of life [3, 4]. Down syndrome (DS) is a genetic disorder that results from a constitutional trisomy of chromosome 21. This disorder is associated with distinguishing phenotypic features, intellectual disability, co-occurring structural birth defects, and an increased risk for CHC. Children with DS are also at increased risk for developing hematologic malignancies, with a 10 to 20-fold excess risk in comparison with the general population, so that between 1:100 and 1:150 children with DS will develop acute leukemia (AL), [5, 6] predominantly B-lineage acute lymphoblastic leukemia (ALL) or acute myeloid leukemia (AML), composing 2% of all pediatric ALL cases and 15% of all pediatric AML cases. During treatment for AL, children with DS experience excess acute cancer therapy-related toxicities compared to their non-DS peers with ALL and AML [7–9].

In the absence of DS, AL treatment confers a substantial risk for late effects. Among 272 AML survivors enrolled to the Childhood Cancer Survivor Study (CCSS), the cumulative incidence of CHC at 20 years from diagnosis was 50%, of which 16% were severe, compared with only 6% of sibling controls [10]. Similarly, at 25 years from diagnosis, the cumulative incidence of CHC among ALL survivors enrolled to CCSS was 65%, of which 21% were graded as severe [11]. A meta-analysis of neurocognitive sequelae of childhood ALL provides consistent evidence that cancer therapy impacts intellectual function even in the absence of radiation exposure, particularly with respect to attention, working memory, and processing speed [12, 13], although less is known regarding the neurocognitive sequelae of AML treatment [14].

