### Recruitment, population, and eligibility

A unique feature of this observational survivorship trial is the hybrid recruitment approach that leverages the COG Childhood Cancer Research Network (ACCRN07) and Project EveryChild (APEC14B1) research registration and biobanking protocols [33, 34]. Potential participants with DS-AL are identified and recruited by two mechanisms run in parallel: 1) The Coordinating Center conducts centralized recruitment of patients that have consented to recontact and were enrolled to either ACCRN07, APEC14B1, and/or AEPI20N2 The DS-ALL Deep Phenotyping Project: Evaluating the Association Between Co-occurring Birth defects and ALL Risk in DS; 2) Site-based prospective recruitment at COG sites that have activated the study protocol (only for subjects not enrolled to any of the above registries or studies).

Eligible survivors are those with DS-AL who are ≥ 6 years old and < 40 years old, in remission, at least 36 months off primary cancer treatment, and able to understand either English or Spanish. Bone marrow transplant recipients are excluded (see Table 2). A diagnosis of Down syndrome is required and may include any of the three recognized types: trisomy 21 resulting from chromosomal nondisjunction (most common), translocation (the patient has 46 chromosomes, but all or part of an additional copy of chromosome 21 is attached to another chromosome), or mosaicism (trisomy 21 that is present in only a fraction of cells). All participants to ALTE22C1 must be a survivor of either ALL or AML/myeloid leukemia of DS (ML-DS) requiring treatment with chemotherapy and may not have had any other cancer diagnosis other than transient abnormal myelopoiesis. Based on the racial and ethnic distribution of childhood leukemia in the United States, the sample is expected to be 70% White, 10% Black, 20% other or multi-race, and about 20% Hispanic (estimates derived from the Surveillance Epidemiology and End Results Program).

**Table 2 Tab2:** Eligibility Criteria for COG ALTE22C1

Inclusion Criteria
• Age ≥ 6 and < 40 years at the time of enrollment
• Diagnosis of Down syndrome
• Survivor of ALL or AML treated with chemotherapy for their cancer diagnosis
• Completed treatment at least 36 calendar months prior to enrollment
• Life expectance > 1 year
• English or Spanish speaking
Exclusion Criteria
• History of hematopoietic stem cell transplant
• History of another cancer either prior to or subsequent to the ALL/AML diagnosis

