## Discussion

ALTE22C1 is an ongoing multisite study open through the COG cooperative group that will compare the CHC and neurocognitive outcomes in DS-AL survivors, compared to persons with DS and no cancer history. The hybrid recruitment design leverages both COG patient registries as well as site-based recruitment of non-registry participants, thus supporting the collection of both patient-reported outcomes and data from in-person clinical assessment, in addition to reducing potential selection bias associated with exclusively registry-based recruitment. The steady pace of accrual since study launch suggests support from a motivated patient population as well as suggesting benefit to a study design that supports remote participation and that minimizes burden on participating COG sites.

There is a substantial dearth in our understanding of the long-term impact of cancer treatment in this vulnerable population. To date, the published data have compared late effect prevalence in this at-risk population to non-DS survivors of AL, which disregards the effect of the baseline excess risk for CHC experienced by individuals with DS. For example, the CCSS compared CHC in 154 DS-AL survivors to non-DS survivors matched by diagnosis, age at diagnosis, race/ethnicity, sex, radiation, and chemotherapy exposures, indicating that DS-AL survivors (median age 20 years, range 10–48 years) were at greater risk for serious CHC and ≥ 3 CHC than non-DS AL survivors, with a 25 year CHC cumulative incidence of 83% vs. 69% [49]. Similar results were seen in a smaller cohort of DS-AML survivors [50]. One study evaluated neurocognitive outcomes in DS-AL survivors vs. DS children without AL and found greater deficits in verbal intelligence, spelling, receptive and expressive vocabulary, visual-motor skills, and adaptive function [39]. In a more recent study that compared neurocognitive outcomes between 117 DS controls and 43 DS-AL survivors, differences were observed between the groups in completion rates for executive function and processing speed measures as well as in performance and rating measures of executive function [51].

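### The external comparison of CHC prevalence with non-DS leukemia survivors fixes no common time since diagnosis, so where follow-up is shorter than in the published figures a true DS-AL excess is understated and may be hidden or reversed

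*Protocol article*

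**What the plan says.** The Statistical analyses section opens the Part 1 plan with an external comparison: "the prevalence for each CHC will be estimated and compared with published CHC prevalence and grading data from non-DS AL survivor cohorts". It names references 10, 11, 43 and 44 as sources and CTCAE as the grading system. No time horizon, standardization or adjustment is attached to this step.

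The Background describes two of the four sources. For AML survivors (reference 10), "the cumulative incidence of CHC at 20 years from diagnosis was 50%, of which 16% were severe". For ALL survivors (reference 11), "at 25 years from diagnosis, the cumulative incidence of CHC among ALL survivors enrolled to CCSS was 65%, of which 21% were graded as severe". Both are fixed-horizon cumulative incidences of any CHC. References 43 and 44 are cited without description.

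Table 2 admits survivors aged 6 to under 40 who meet the criterion "Completed treatment at least 36 calendar months prior to enrollment".

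The pooled logistic and Cox models that follow in the same section estimate the effect of a leukemia diagnosis on CHC, which is the contrast with DS controls. The stated covariate adjustment applies to those models. The data collection section says that dates of CHC onset are abstracted. The Abstract's Discussion promises results against both non-DS leukemia survivors and DS controls.

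**The concern.** The proportion of a cohort affected so far depends on how long its members have been followed. A cumulative incidence at 20 or 25 years refers to one fixed, long follow-up. Setting the first against the second mixes the effect of DS with the effect of time since diagnosis.

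Eligibility alone makes some mismatch certain: anyone enrolled before age 20 has less than 20 years since diagnosis, and anyone enrolled before age 25 has less than 25.

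At stake is the contrast with non-DS survivors that the Abstract advertises. The closing Discussion expects the results to inform surveillance, and notes that current long-term follow-up guidelines take no account of DS status. An unaligned comparison could suggest that DS-AL survivors fare no worse than other leukemia survivors when they do.

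**Working it through.** The article gives no expected value or power for this comparison, so there is no stated figure to reproduce. The check asks what an unaligned comparison would show if the article's own matched figures were true.

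**Inputs.** The Discussion reports a matched comparison of DS-AL and non-DS AL survivors "with a 25 year CHC cumulative incidence of 83% vs. 69" per cent. This is for any CHC, with ALL and AML combined. It is used because both groups share one horizon. The study it comes from is not among the four named comparators, so 69% stands in for a published 25-year figure.

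**Assumptions.** Constant hazard from diagnosis; prevalence read as the proportion ever affected; competing death ignored; follow-up assumed, because the article does not give it.

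**Step 1, hazards.** λ = −ln(1 − F)/t.
- DS-AL: −ln(0.17)/25 = 0.0709 per year.
- Non-DS AL: −ln(0.31)/25 = 0.0468 per year.
- Ratio: 0.0709/0.0468 ≈ 1.51.

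**Step 2, proportion affected at time T.** P(T) = 1 − exp(−λT).

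| T (years) | DS-AL | Non-DS AL, same T | Aligned difference | DS-AL minus 69% |
|---|---|---|---|---|
| 10 | 50.8% | 37.4% | +13.4 | −18.2 |
| 15 | 65.5% | 50.5% | +15.0 | −3.5 |
| 25 | 83.0% | 69.0% | +14.0 | +14.0 |

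**Step 3, break-even.** DS-AL prevalence reaches 69% at T = 25 × ln(0.31)/ln(0.17) = 16.5 years. With Weibull hazards through the same two 25-year points, T = 25/1.513^(1/k), which gives about 14 years for shape k = 0.7 and 19 years for k = 1.5.

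**Step 4, mixed follow-up.** For follow-up uniform between a and c years, the mean is 1 − [exp(−λa) − exp(−λc)]/[λ(c − a)].

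| Assumed range (years) | DS-AL | Non-DS AL, same range | Aligned difference | DS-AL minus 69% |
|---|---|---|---|---|
| 4–15 | 47.7% | 35.2% | +12.5 | −21.3 |
| 5–20 | 56.8% | 43.2% | +13.6 | −12.2 |
| 4–25 | 60.8% | 47.2% | +13.6 | −8.2 |
| 5–30 | 67.1% | 53.4% | +13.7 | −1.9 |
| 5–35 | 70.9% | 57.5% | +13.4 | +1.9 |

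In every row the aligned excess is 12 to 14 points. The unaligned difference is negative in the first four rows, though only slightly in the fourth. In the last it has the right sign but shows about 2 points instead of 13.

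**Step 5, the figures quoted for the named sources.** On the same DS-AL hazard, break-even is 14.8 years against 65% (ALL, 25 years) and 9.8 years against 50% (AML, 20 years). These set a combined DS-AL figure against a single leukemia type, so they show sensitivity only.

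**The case against.** The strongest reply is that the plan speaks of published prevalence and grading data for each CHC, and the 50% and 65% appear only as Background motivation. A reader might infer that all the comparators are 20- and 25-year cumulative incidences. The article does not support that: two of the four sources are not described, and it does not say which figures from the other two will be used. The quoted percentages are also for any CHC, so the distortion for an individual condition cannot be sized. This stands, and it is why the point is limited to the missing alignment and the sizes are only illustrations.

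A reader might also infer that the comparison will certainly make DS-AL survivors look healthier. That does not follow. Eligibility runs to under 40 years, and with long follow-up the sign does not reverse. The illustration also starts risk at zero at diagnosis. If conditions present before leukemia are counted, DS-AL prevalence would be higher than modeled; the article does not say whether they are.

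Excluding transplant recipients and people with another cancer might seem to bias the contrast further. That depends on how the published cohorts treated both, which the article does not report, so nothing is claimed here.

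Finally, the contrast is not the primary one, has no test or power attached, and its details may sit in a fuller document. That lowers the stakes. It does not remove the point: the article itself names prevalence as the survivor measure, names the comparator sources, and reports two of them only at fixed horizons. The adjusted models that follow serve the DS-control contrast and do not repair this step.

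**Conclusion.** The point holds in limited form. As written, the external comparison has no common time since diagnosis, and the only figures given for two of its four sources are fixed-horizon cumulative incidences of any CHC. Where survivors' follow-up is shorter than the published horizon, a true DS-AL excess is understated and may be hidden or reversed.

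Under constant hazards fitted to 83% and 69% at 25 years, a true hazard ratio of about 1.5 appears as a deficit until roughly 16.5 years of follow-up (about 14 to 19 years across the Weibull shapes tried). Beyond that, and up to 25 years, it appears as a reduced excess. These sizes rest on any-CHC figures and an assumed follow-up distribution; they do not predict the result for any single condition.

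The primary comparison with DS controls is not affected. The change should be made because the non-DS contrast is promised in the Abstract and the data needed to align it are already collected.

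**What to change.** Use the abstracted onset dates to estimate cumulative incidence in DS-AL survivors by time since diagnosis, separately for ALL and AML. Compare each estimate with the published figure at the same time point. Alternatively, where the sources give rates, apply them to DS-AL person-years and report observed/expected ratios. State which figure is taken from each of the four sources and at what horizon. Label any prevalence comparison that cannot be aligned as descriptive.

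The cost is a modest amount of extra analysis and no new data. The downside is imprecision at longer time points, where few survivors may have enough follow-up; confidence intervals should be shown, and a shorter horizon used where the published source allows it.

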## Methods/design

### Aims

The primary aim of this study is to determine the prevalence, type, and severity of CHC in survivors of DS-AL and to compare CHC outcomes to those of frequency-matched individuals with DS with no cancer history. Secondary aims include characterizing post-treatment clinical outcomes of DS-AL, determining prevalence and severity of parent-reported neurocognitive outcomes in survivors of DS-AL compared with frequency-matched individuals with DS without leukemia, determining health-related quality of life in survivors of DS-AL, and identifying clinical risk determinants of CHC, neurocognitive outcomes, and clinical outcomes in survivors of DS-AL. Biological and molecular correlations will be tested in exploratory aims, i.e., we will test whether structural birth defects and genetic alterations associated with etiology also demonstrate associations with CHC in DS-ALL, and whether telomere length is associated with in-person-assessed neurocognitive outcomes in DS-ALL.

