• Parent or guardian unable to complete the required forms

The comparison population (‘DS controls’) are active participants in an ongoing research study cohort of children and young adults with DS. Recruitment to this study began in 1989 as a population-based case–control study conducted in the five-county metropolitan area of Atlanta and has since expanded recruitment to sites across the United States. Recruitment and enrollment methods to this study are described previously [35–38]. Controls will be frequency-matched to cases by age, sex, and, when possible, race and ethnicity.

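### The Part 1 CHC models name no pre-leukemia or cohort term, so a survivor–control difference that predates leukemia cannot be told apart from an effect of AL

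*Protocol article*

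**What the plan says.** The primary aim (Aims) is to "compare CHC outcomes to those of frequency-matched individuals with DS with no cancer history". The abstract adds that the comparison cohort excludes people with cancer.

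Under Statistical analyses, survivors and controls enter pooled logistic and stratified Cox models, "using two modeling approaches [45] to account for time-varying independent variable (diagnosis with AL) effects". Age is the time axis: "we will pool observations over equal length intervals of chronologic age to predict short term risk of CHC during each age interval". Hazard ratios are to be estimated within each age interval and reported as effects of ALL, AML or any AL. On covariates the text says: "All models will be adjusted for age, sex, race/ethnicity, and relevant cancer or DS characteristics". It names neither a survivor/control indicator nor a separate level for survivors' time before AL.

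Controls are "active participants in an ongoing research study cohort of children and young adults with DS", frequency-matched on age, sex and, when possible, race and ethnicity (Recruitment, population, and eligibility). Survivors come from oncology registries and sites. One recontact source is "The DS-ALL Deep Phenotyping Project: Evaluating the Association Between Co-occurring Birth defects and ALL Risk in DS". Among the exploratory aims, "we will test whether structural birth defects and genetic alterations associated with etiology also demonstrate associations with CHC in DS-ALL".

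**The concern.** A time-varying diagnosis is 0 until the diagnosis date. On an age axis, a survivor's years before AL therefore sit at the same level as control years, which has two consequences.

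First, the reference is a mixture: matched controls plus children who later developed AL and were sampled for that reason. The aim names only the former.

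Second, the AL coefficient reads as an effect of leukemia only if future survivors and controls had the same CHC hazard beforehand. The cohorts differ in recruitment source, possibly in ascertainment, and possibly in predisposition, which the exploratory aim takes seriously enough to study. Without a term for pre-AL survivor time, the model cannot show whether the groups already differed, although onset dates and birth defects are collected in both.

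**Working it through.** **Inputs from the article (Sample size and power calculations).** Baseline hazard 0.062; two-sided alpha 0.05; 200 v 200 for ALL with 80% power at hazard 0.046 or 0.084; 100 v 100 for AML at 0.040 or 0.096.

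**The plan's own figure.** Neither event count nor follow-up is given, so the 80% cannot be rebuilt directly. The Schoenfeld formula gives the events it implies: d = 4(1.96 + 0.8416)² / (ln HR)².
- 0.084/0.062 = 1.355: 31.40/0.0922 = 341 of 400.
- 0.046/0.062 = 0.742: 31.40/0.0891 = 353 of 400.
- 0.096/0.062 = 1.548: 165 of 200. 0.040/0.062 = 0.645: 164 of 200.

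This point does not dispute that figure. It uses 1.355 as a difference the study is designed to detect.

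**Why a prior difference passes into the AL term.** Let r be the survivor/control hazard ratio at all ages, with no AL effect, and w the survivors' share of reference time in an age interval. The single-term ratio is then HR = r / (1 + w(r − 1)).
- Where w = 0 (ages past the last AL diagnosis), HR = r = 1.355.
- Where w = 0.5, HR = 1.355/1.1775 = 1.15.

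So merging pulls the ratio toward 1. It does not create the bias.

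**Simulation.** Constant hazard 0.062, true AL effect 1, r = 1.355, age-stratified piecewise-exponential models. Assumed, not in the documents: enrollment age uniform over 6–40, AL age uniform over the range shown, about 2 years of therapy. Ratios are from 300,000 per group; rejection rates are from 400 runs of 200 v 200.

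| AL age (y) | Survivor share of reference time | Single AL term: HR | Rejects | Pre-AL time dropped: HR | Post- v pre-AL, with pre-AL level: HR | Rejects |
|---|---|---|---|---|---|---|
| 0.5–4 | 14.6% | 1.325 | 65% | 1.354 | 0.995 | 4% |
| 1–8 | 22.7% | 1.301 | 54% | 1.351 | 0.995 | 6% |
| 1–15 | 28.9% | 1.259 | 41% | 1.341 | 0.992 | 6% |

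Other prior ratios: r = 1.2 gives a single-term HR of 1.15–1.19, and r = 1.5 gives 1.38–1.46. With r = 1 the term is unbiased (1.00) and rejects in 3–4%. A repeat at 200 v 200 with r = 1.355 gave HR 1.25–1.33, rejecting in 37–62%.

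**What three states give at 200 v 200.**
- *Post-AL v control.* It still carries the full prior difference (HR 1.32–1.36 when r = 1.355). With a true AL HR of 1.355 and no prior difference, the SE of the log HR moves from 0.123 to 0.124, 0.130 to 0.132 and 0.139 to 0.142, that is +0.8%, +1.5% and +2.2%; across all runs about 1–4%. Power changes by one point (71 to 70%, 61 to 60%, 62 to 61%).
- *Pre-AL v control.* It estimates r directly, with power of only about 22–49% at r = 1.355.
- *Post-AL v pre-AL.* It is the ratio of the two contrasts above, so a constant r cancels. The SE is 0.18–0.27, so the 95% CI runs from the estimate divided by to multiplied by exp(1.96 × 0.18) = 1.42 up to exp(1.96 × 0.27) = 1.70. For a true AL HR of 1.355, power is about 17–45%, against 60–70% for the single term.

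**The case against.** **No prior difference is documented.** This stands. The exploratory hypothesis concerns associations within DS-ALL and does not say that survivors differed from controls before leukemia. A reader might infer that the planned HR is biased; the documents support only that a bias, if present, would go unseen.

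**Merging is not the cause.** This stands. A reader might infer that taking pre-AL years out of the reference cures the problem. It does not: dropping them gives 1.34–1.35 rather than 1.26–1.33, and post-AL versus control in the three-state model still holds the full difference. That is ordinary between-cohort confounding, and it affects any comparison of these two groups.

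**The contrast that removes a constant difference is weak.** This stands. Past the last age at AL there is no pre-AL time, so post- versus pre-AL must carry an early-childhood ratio forward to as late as age 40. Letting the conclusion depend on whether the pre-AL ratio is significant would switch the estimand on a low-powered test.

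**The coding is inferred, and detail may sit elsewhere.** This stands in part. The article does not say in words that pre-AL years join the reference, and the cited method is not at hand. But the exposure and its labelling as an effect are stated, and the ordinary reading of a time-varying diagnosis on an age axis gives that pooling. Adjusting for DS characteristics could include birth defects and remove part of a difference. It would not cover recruitment source or ascertainment.

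**Conclusion.** The point holds in a limited form. As described, the models do not use the aim's comparator as their reference, and they have no term that would separate a difference predating leukemia from an association with leukemia. If the prior ratio were 1.355 and AL had no effect, the planned term would report about 1.26–1.33 and reject in 41–65% of studies of 200 v 200; if the prior ratio were 1, it would be unbiased.

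These sizes rest on the assumed AL ages, a constant hazard of 0.062, a prior ratio constant over age, and one AL coefficient across ages. Interval-specific ratios beyond the last AL age would carry the full prior ratio. The documents do not support saying that a prior difference exists, or that merging the person-years produces the bias. The change is worth making because it is cheap, restores the stated comparator and makes a hidden assumption visible.

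**What to change.** 1. In both the pooled logistic and Cox models, code a three-level time-varying state: control (reference), survivor before AL, survivor after AL.
2. Keep post-AL versus control as the main contrast and describe it as an association, not an effect.
3. Beside it, report pre-AL versus control as an estimate with 95% CI: a negative-control check limited to ages at which pre-AL time exists. Do not use it as a pass/fail test.
4. Report post-AL versus pre-AL as a sensitivity analysis only. State that it assumes the pre-AL ratio carries forward to later ages, and do not switch the conclusion on a significance test.

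Cost: one extra model term, no new data, and about 1–4% larger SE on the main contrast. The two added contrasts are imprecise (SE of log HR about 0.15–0.27 under AL ages of 0.5–4 to 1–15 years and hazard 0.062). A pre-AL ratio near 1 with a wide interval would therefore not show that the groups were alike.
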